### Sample size

The primary efficacy analysis will assess the non-inferiority of the clinical response of Gram stain-guided antibiotic therapy compared with standard therapy. The margin of non-inferiority is set at 20% on the basis of statistically acceptable tolerance and clinically acceptable margin. This margin was used in previous large clinical trials in the field of critical care [19–21]. Then, the non-inferiority of Gram stain-guided antibiotic therapy is concluded if the upper limit of the one-sided 97.5% CI for the difference in clinical response (standard – Gram stain-guided) is less than 20%. To achieve a power of 80% with an α level of 5%, assuming as stated in the previous study that the clinical response rate is 67.8% with standard therapy and is the same with Gram stain-guided antibiotic therapy (unpublished data), with a non-inferiority margin of − 20%, 86 patients are needed in each group. Assuming 10% non-evaluable patients, we decided to enrol 100 patients per group.

### Statistical analysis

Because this is a non-inferiority trial, we will compare the proportion of patients meeting the definition of clinical response using per-protocol analysis as a primary analysis. The per-protocol analysis population will consist of all randomised patients who are not lost to follow-up and have no major protocol deviations. We will also conduct an intention-to-treat analysis as a secondary analysis. We will attest the non-inferiority of the primary outcome on the basis of the normal theory test for binomial proportions. We will conduct the primary analysis without adjustment of potential confounders. We will construct multivariable logistic models or Cox proportional models including the stratified variables as the secondary analysis. We will conduct other post hoc exploratory analyses based on the recommendations of the steering committee. Because of the exploratory nature of these analyses for other than the primary endpoint, no correction for multiplicity is made.

Secondary outcomes will be analysed under a superiority or non-inferiority assumption, as appropriate. Pre-defined subgroup analyses for the primary and secondary endpoints include (1) patients who received prior antibiotic therapy during the hospitalisation versus those who did not, (2) length of ICU stay ≥ 5 days versus < 5 days before randomisation, and (3) septic shock versus no septic shock.

All *P* values are two-sided, and *P* < 0.05 is considered significant other than for the non-inferiority test for clinical response, for which a one-sided *P* < 0.025 is considered significant. All statistical analyses will be performed using JMP 13.1 and SAS 9.4 software (both from SAS Institute Inc., Cary, NC, USA).

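### Non-inferiority can be concluded from the per-protocol set alone; the intention-to-treat result is planned but cannot change the conclusion

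*Protocol article*

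**What the plan says.** All references are to the protocol article.

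- **Primary set.** Statistical analysis: "we will compare the proportion of patients meeting the definition of clinical response using per-protocol analysis as a primary analysis". The reason given is that this is a non-inferiority trial.
- **Definition of that set.** Same section: "all randomised patients who are not lost to follow-up and have no major protocol deviations".
- **Role of ITT.** Same section: "We will also conduct an intention-to-treat analysis as a secondary analysis".
- **Decision rule.** Sample size: non-inferiority is concluded if "the upper limit of the one-sided 97.5% CI for the difference in clinical response (standard – Gram stain-guided) is less than 20" per cent. The test level is given under Statistical analysis: "a one-sided *P* < 0.025 is considered significant".
- **Blinding.** Design: treatment is open-label and endpoint assessment is blinded. Outcome measures: blinded evaluators judge the primary outcome from data that the site investigators collect.
- **Treatment rules.** Trial interventions: standard-arm patients receive the two-agent combination, while Gram stain-arm patients may receive narrower initial cover. Changes of treatment on culture results are permitted in both arms.
- **Expected losses.** Sample size: 86 evaluable patients per group, 10% non-evaluable, 100 enrolled per group.

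No sentence says what is concluded if the per-protocol and ITT results disagree. As the rule is written, the per-protocol result decides.

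**The concern.** Per-protocol analysis guards against one bias in a non-inferiority trial: under ITT, departures from assigned treatment can dilute a real difference. It opens the door to another. Both grounds for exclusion arise after randomisation, so the patients left in the two arms need not be comparable. Neither set is conservative in every circumstance.

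Two features of this trial make selective exclusion plausible. Clinicians know the arm, and blinded adjudication protects how outcomes are classified but not who deviates or is lost. The strategies also differ in which departures are possible: initial cover broader than the stain indicates is essentially a Gram stain-arm departure, whereas leaving out one of the two agents is the obvious standard-arm departure. If the excluded patients differ in prognosis between arms, the per-protocol difference no longer estimates the randomised one.

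At stake is a positive conclusion for narrower initial treatment in ventilated patients, reached while the comparison of everyone randomised does not rule out a 20-point deficit.

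**Working it through.** **Step 1. Inputs.**

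- From Sample size: margin 20 points ("The margin of non-inferiority is set at 20% on the basis of statistically acceptable tolerance and clinically acceptable margin"); 67.8% response in both arms ("the clinical response rate is 67.8% with standard therapy and is the same with Gram stain-guided antibiotic therapy (unpublished data"); 80% power; 86 evaluable and 100 enrolled per group; 10% non-evaluable.
- From Statistical analysis: one-sided 0.025 and a normal-theory test.
- Assumed here, because no document gives it: who is excluded and how those patients respond. Ranges are shown.

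**Step 2. The plan's own figure.**

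n = (1.960 + 0.842)² × 2 × 0.678 × 0.322 / 0.20² = 7.849 × 0.4366 / 0.04 = 85.7, so 86 per group. The plan's figure is reproduced. A one-sided 5% would give 68, so the Sample size wording, "To achieve a power of 80% with an α level of 5" per cent, must mean two-sided 5%, which agrees with the one-sided 2.5% used elsewhere. Allowing for losses, 86 / 0.9 = 95.6, so 96, rounded up in the plan to 100.

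**Step 3. Can a failed ITT result pass per-protocol?**

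Upper limit = (pS − pG) + 1.960 × √[pS(1 − pS)/nS + pG(1 − pG)/nG], where S is standard and G is Gram stain-guided. The counts are illustrative.

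| Set | Standard | Gram stain | Difference | Standard error | Upper limit | Below 20%? |
|---|---|---|---|---|---|---|
| ITT | 68/100 | 60/100 | 8.0 | 6.76 | 21.3% | no |
| Three Gram stain failures excluded | 68/100 | 60/97 | 6.1 | 6.79 | 19.4% (19.45) | yes |
| ITT | 68/100 | 58/100 | 10.0 | 6.79 | 23.3% | no |
| Ten Gram stain failures excluded | 68/100 | 58/90 | 3.6 | 6.87 | 17.0% | yes |
| As above, and five standard failures excluded | 68/95 | 58/90 | 7.1 | 6.85 | 20.6% | no |
| Ten excluded per arm: standard 7 responders and 3 failures, Gram stain 2 responders and 8 failures | 61/90 | 56/90 | 5.6 | 7.10 | 19.5% | yes |

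The last row compares with the second ITT row: equal numbers excluded, within the planned 10%, can still reverse the result if the outcome mix differs between arms.

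**Step 4. Effect on the error rate.**

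Take a true ITT deficit of exactly 20 points (67.8% versus 47.8%). If a fraction g of an arm's failures is excluded, its per-protocol response rate becomes p / [p + (1 − p)(1 − g)]. For example, with g = 0.2 in the Gram stain arm only: 0.478 / (0.478 + 0.522 × 0.8) = 0.534, so the per-protocol difference is 0.678 − 0.534 = 14.4 points. The false-conclusion rates come from 1,000,000 simulated trials with 100 per arm.

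| Exclusion pattern (assumed) | True per-protocol difference | False non-inferiority, per-protocol alone |
|---|---|---|
| Random, 10% of each arm | 20.0 | about 2.4% |
| 10% of failures, both arms | 19.6 | about 2.8% |
| 20% of failures, both arms | 19.1 | about 3.3% |
| 10% of failures, Gram stain arm only (about 5 patients) | 17.4 | about 5.5% |
| 20% of failures, Gram stain arm only (about 10 patients) | 14.4 | about 12% |
| 10% of failures, standard arm only | 22.3 | below nominal |
| 20% of failures, standard arm only | 24.7 | below nominal |

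With 10% excluded from each arm, at random in the standard arm, the rate rises with the share of Gram stain-arm exclusions that are failures: 2.4% at 52% (random), 4.5% at 70%, 6.1% at 80% and 10.9% at 100%.

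**Step 5. Requiring both sets.**

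- *Error rate.* With 5% or 10% of the Gram stain arm excluded, all of them failures, per-protocol alone gives 5.2% or 10.9%. Requiring both sets gives 2.4% or 2.5%.
- *Power* at 67.8% in both arms, 100 per arm and 10% excluded on average: per-protocol alone 82%. Both sets: 78% if excluded patients count as ITT failures, 80% if they respond like the rest. With exactly ten excluded per arm, runs give 80% to 82%.

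**The case against.** The strongest defence is that this is a declared choice with a stated reason. ITT can itself be anti-conservative in a non-inferiority trial, and per-protocol primary with ITT also reported is a known approach. ITT is prespecified, so disagreement would be visible to any reader. That stands: the plan neither ignores ITT nor contradicts itself. It does not answer the point that a visible ITT failure would not alter the conclusion.

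The size of the effect also needs restraint. A reader might infer that exclusions will fall on sicker patients in the Gram stain arm only. The documents do not support that. The article does not define a major deviation, which the full protocol or analysis plan may do; some broadening of treatment in the Gram stain arm is permitted; and standard-arm deviations, departures from the minimum treatment duration and loss to follow-up are all possible too. A reader might likewise infer that the one-sided 2.5% level is already lost. It is lost only under some patterns. Random exclusion leaves it intact, equal selection in both arms barely moves it, and selection in the standard arm makes the test stricter.

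Nor is there a finding in deaths before the follow-up visit, or in blinded review and tabulation of deviations. The outcome definition already points to non-response for a patient who dies before that visit, and the rest is ordinary analysis-plan content.

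**Conclusion.** The point holds in a limited form. The protocol fixes the per-protocol set as the sole basis for the conclusion and gives ITT no say, so a result that fails among all randomised patients can be declared non-inferior. Three selectively excluded patients are enough in a plausible example, well inside the planned 10%.

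The effect on the error rate is conditional. At a true 20-point deficit it runs from about 2.4% to about 12% over the patterns from random exclusion to removal of 20% of Gram stain-arm failures, and falls below nominal if the selection is in the standard arm. These figures rest on the plan's 67.8%, on 100 per arm and on assumed outcomes among the excluded. They show what the rule allows, not what will happen. This is a weakness in the decision rule that can be removed cheaply, not a demonstrated failure of the design.

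**What to change.** State in Sample size and in Statistical analysis that non-inferiority is concluded only if the upper limit of the one-sided 97.5% confidence interval (standard minus Gram stain-guided) is below 20% in both the ITT and the per-protocol sets. Per-protocol may remain the first-listed analysis.

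The cost is wording and a little power, with no extra patients in the plan as sized. Power moves from about 82% for per-protocol alone to roughly 78–82% for both, depending on how excluded patients respond and how they are counted in ITT. A reader might assume that power stays above 80%; the calculations do not guarantee it, so the plan should state about 80%.

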**Methods/design:**

The GRACE-VAP trial is a multicentre, randomised, open-label parallel-group trial to assess the non-inferiority of Gram stain-guided initial antibiotic treatment to guidelines-based initial antibiotic treatment for the primary endpoint of clinical response rate in patients with VAP. Secondary endpoints include the coverage rates of initial antibiotic therapies, the selected rates of anti-pseudomonal agents and anti-methicillin-resistant *Staphylococcus aureus* (anti-MRSA) agents as initial antibiotic therapies, 28-day all-cause mortality, ICU-free days, ventilator-free days and adverse events. Patients are randomly assigned to receive Gram stain-guided treatment or guidelines-based treatment at a ratio of 1:1. In the Gram stain group, results of Gram staining of endotracheal aspirate are used to guide the selection of antibiotics. In the guidelines group, the combination of an anti-pseudomonal agent and an anti-MRSA agent is administered. A total sample size of 200 was estimated to provide a power of 80% with a one-sided alpha level of 2.5% and a non-inferiority margin of 20%, considering 10% non-evaluable patients.

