### Randomisation and allocation concealment

Patients are randomly allocated to each treatment arm at a 1:1 ratio no earlier than 1 day before starting antibiotic therapy for VAP. Randomisation will be performed with the use of a stochastic minimisation procedure stratified by study centre, presence of chronic obstructive pulmonary disease, presence of traumatic brain injury, presence of post-cardiopulmonary arrest syndrome, and prior antibiotic therapy during the hospitalisation. We will use an electronic data capture system to conduct randomisation and data collection.

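### The primary test leaves out the five minimisation factors, so it is somewhat conservative and forgoes precision; a risk difference adjusted for them should be pre-specified

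*Protocol article*

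**What the plan says.** Under Randomisation and allocation concealment, patients are allocated 1:1 by a "stochastic minimisation procedure stratified by study centre, presence of chronic obstructive pulmonary disease, presence of traumatic brain injury", together with post-cardiopulmonary arrest syndrome and prior antibiotic therapy in the same hospital stay. That makes five factors.

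Under Statistical analysis, the primary comparison is a normal-approximation test of two proportions in the per-protocol set, with intention-to-treat as secondary. On covariates the text is explicit: "We will conduct the primary analysis without adjustment of potential confounders". The factors return only later: "We will construct multivariable logistic models or Cox proportional models including the stratified variables as the secondary analysis".

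Under Sample size, the decision rule is on the absolute scale. Non-inferiority is concluded if the "upper limit of the one-sided 97.5% CI for the difference in clinical response (standard – Gram stain-guided) is less than 20"%. The planning assumption is that "the clinical response rate is 67.8% with standard therapy and is the same with Gram stain-guided antibiotic therapy".

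**The concern.** Minimisation makes the arms alike on its factors. Where those factors predict response, the difference between arms varies less from trial to trial than the simple two-proportion formula assumes. A test that ignores the factors uses the larger variance. Its interval is then wider than it need be, and its actual one-sided error lies below the nominal 2.5%. The sponsor presumably chose the factors because it expected them to matter. The absence of adjustment is a stated choice, so it is not a detail left to an analysis plan that is not shown.

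A second, smaller matter is the scale. The margin is 20 percentage points. The adjusted models named naturally yield odds ratios or hazard ratios, and the article does not say that they will also be expressed as a risk difference. If the adjusted and unadjusted results seemed to differ, nothing stated says how the adjusted one bears on the margin.

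At stake are some precision and a clear adjusted check. The validity of the non-inferiority conclusion is not.

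**Working it through.** **Inputs from the protocol article.** Response is 67.8% in both arms and the margin is 20 points. The test is one-sided at 2.5% ("for which a one-sided *P* < 0.025 is considered significant"). The article states 86 evaluable per group and 100 enrolled per group, with 10% non-evaluable, which leaves 90 per arm.

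**Assumed.** R² is the share of response variance explained by the five factors. The article does not give it, so a range is used.

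**Step 1: the plan's own figure.**
n = 2 × 0.678 × 0.322 × (1.960 + 0.842)² / 0.20² = 85.7, so 86 per group. The stated figure reproduces with no covariate term, so the sample size and the unadjusted test agree with each other.

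**Step 2: standard error at 90 per arm.**
SE = √(2 × 0.678 × 0.322 / 90) = 0.0697, and 0.20 / SE = 2.871. With R² = 0, power = Φ(2.871 − 1.960) = Φ(0.911) = 81.9%.

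**Step 3: effect of balance.** If the factors are balanced, the true standard deviation of the difference is SE × k, with k = √(1 − R²).

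- One-sided error of the unadjusted test: Φ(−1.960 / k)
- Power of the unadjusted test: Φ(0.911 / k)
- Power of an adjusted risk difference: Φ(2.871 / k − 1.960)

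| R² | k | Error, unadjusted | Power, unadjusted | Power, adjusted | Gain (points) |
|---|---|---|---|---|---|
| 0 | 1 | 2.5% | 81.9% | 81.9% | 0 |
| 0.05 | 0.975 | 2.2% | 82.5% | 83.8% | 1.3 |
| 0.15 | 0.922 | 1.7% | 83.9% | 87.6% | 3.7 |

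**Step 4: the gain in patients.** The unadjusted test matches the adjusted power at m per arm when 0.20 / SE(m) = 2.871 + 1.960 × (1 − k). Hence m = 90 × [(2.871 + 1.960 × (1 − k)) / 2.871]².

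- R² = 0.05: m = 90 × (2.921 / 2.871)² = 93.1, or 3.5% more.
- R² = 0.15: m = 90 × (3.024 / 2.871)² = 99.8, or 11% more.

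**Step 5: simulation of minimisation.** This used 172 evaluable patients, with 12 centres, a biased coin of 0.8 and the factor effects all assumed, and 2,500 runs per scenario. The adjusted analysis was a logistic model standardised to a risk difference.

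- R² about 0.13: the unadjusted SE averaged 0.0708 against a true standard deviation of 0.0668, a ratio of 1.06. Power was 82.3% unadjusted and 85.5% adjusted. One-sided error was 2.2% and 2.9%. The Monte Carlo standard error is √(0.025 × 0.975 / 2,500) = 0.3 points, so both are compatible with 2.5%.
- R² about 0.04: power was 80.5% and 81.0%, which is practically equal.

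**Step 6: the scale.** A 20-point loss from 67.8% is an odds ratio of (0.478 / 0.522) / (0.678 / 0.322) = 0.435. The same loss gives 0.444 from a control rate of 60%, 0.407 from 75% and 0.375 from 80%. No single odds ratio stands for the margin.

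**The case against.** The strongest defence is that an unadjusted primary test, fixed in advance, matching the sample-size calculation and erring on the safe side, is a legitimate choice, and that adjusted models are already planned as secondary. Much of this stands, and it rules out several stronger readings.

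- A reader might infer that the trial loses planned power. It does not. Under balance, the power of the unadjusted test rises from 81.9% to 82.5–83.9%. What is given up is a further gain.
- A reader might infer a risk of falsely declaring non-inferiority. With the balance kept, the actual error lies below 2.5%.
- A reader might take 1 / (1 − R²) − 1, that is 5% to 18%, as the saving in patients. That compares the adjusted test with an unadjusted one that gets no benefit from balance, although minimisation supplies that benefit. The fair figure is 3.5% to 11%.
- A reader might infer that the adjusted analysis cannot be set against the margin at all. A logistic model can be standardised to a risk difference. The article does not say that an odds ratio will be the reported measure, and the decision rule does not rest on the secondary models. The Cox model is not tied to the primary endpoint and presumably serves mortality.

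Two further objections limit the size. The gain depends wholly on an R² that the article does not give. The formula also assumes near-complete balance, which the per-protocol set need not keep once patients are excluded after randomisation. The second point cuts both ways: the computed conservatism is a best case, but lost balance is itself a reason for an adjusted check.

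Adjustment is not free either. About 172 × 0.322 = 55 non-responders are expected, against four clinical factors plus the centre terms, so sparse centres must be handled by rule. The simulation does not show that adjustment controls error better.

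**Conclusion.** The point holds as a recommendation on efficiency and clarity. Allocation uses five factors that the primary test expressly leaves out. If they are prognostic, the test is conservative and the interval somewhat too wide, by about 6% in the simulation at R² near 0.13. At 90 per arm the forgone gain is 1.3 to 3.7 points of power for R² of 0.05 to 0.15, and practically nothing at 0.04 or below. These sizes assume the 67.8% response rate in both arms and balance that survives into the analysed set.

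On scale, the supportable statement is narrow: the adjusted models named do not directly give a result in percentage points, and the article does not say that they will be converted. Neither the sample size nor the validity of the non-inferiority rule is in question.

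**What to change.** Pre-specify as the primary estimate a risk difference adjusted for the minimisation factors:

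- Fit a logistic model with treatment, the four clinical factors and centre, and standardise it over the analysed patients to a risk difference, with a robust or delta-method standard error.
- Pool small centres by a rule stated in advance.
- Compare the upper one-sided 97.5% limit with 20% in both the per-protocol and the intention-to-treat sets.
- Keep the unadjusted difference, standard minus Gram stain-guided, as a sensitivity analysis.

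The cost is analysis-plan wording, a few lines of SAS, a modest modelling burden and the pooling rule. No new data are needed, because the factors must be recorded to run the minimisation. If the sponsor prefers to keep the unadjusted test as primary, the minimum change is to state that the secondary logistic model will also be reported as a risk difference with its confidence interval, to be read against the 20-point margin.

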**Fig. 2 Fig2:**
[figure not shown]
Schedule of assessments. *ICU* intensive care unit, *SOFA* Sequential Organ Failure Assessment

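### The planned adjusted models name only the minimisation factors, so no overall treatment estimate adjusted for acute severity is pre-specified, although septic shock must be recorded for a planned subgroup

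*Protocol article*

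**What the plan says.** All references are to the protocol article.

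- **Randomisation and allocation concealment.** Allocation uses a "stochastic minimisation procedure stratified by study centre, presence of chronic obstructive pulmonary disease, presence of traumatic brain injury", and then "presence of post-cardiopulmonary arrest syndrome, and prior antibiotic therapy during the hospitalisation". These are five factors: centre, three conditions and earlier antibiotic exposure.
- **Statistical analysis, primary analysis.** "We will conduct the primary analysis without adjustment of potential confounders".
- **Statistical analysis, adjusted models.** "We will construct multivariable logistic models or Cox proportional models including the stratified variables as the secondary analysis". No other covariate is named.
- **Statistical analysis, subgroups.** One of three pre-defined subgroup comparisons, for primary and secondary endpoints alike, is "septic shock versus no septic shock".
- **Fig. 2 legend (schedule of assessments).** The abbreviation list contains "Sequential Organ Failure Assessment" (SOFA). The figure itself is not shown, so the time of measurement cannot be read.
- The Statistical analysis section also leaves room for further post hoc analyses on the steering committee's recommendation.

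**The concern.** Acute severity at the onset of pneumonia is likely to be prognostic for both clinical response and 28-day mortality. By making septic shock a subgroup factor, the plan itself treats it as relevant. Yet shock is neither a minimisation factor nor a named covariate, and the primary comparison is unadjusted.

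If the arms turn out unequal in shock, readers will ask what the overall difference would be after allowing for it. As the article stands, no pre-specified analysis is named that gives that single figure. It would have to come from the post hoc route, where it carries less weight because the covariate was chosen after the data were seen. A modest gain in precision from a value the trial already needs is also left unused.

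**Working it through.** **Inputs from the protocol (Sample size; Statistical analysis).** Response 67.8% in both arms; margin 20 points; one-sided 2.5% test; 80% power; 86 evaluable patients per arm.

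**Inputs assumed, because the protocol gives neither.** Septic shock prevalence q = 20-40%. Response lower in shock by d = 10-30 points, with the same treatment difference in patients with and without shock.

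**1. The plan's own figure.** n = (1.96 + 0.8416)² × 2 × 0.678 × 0.322 / 0.20² = 85.7, so 86 per arm, as stated. (A one-sided 5% test would need 68, so the 5% in the Sample size section is two-sided.) With 86 per arm, SE = sqrt(2 × 0.678 × 0.322 / 86) = 0.0713, and power = Φ(0.20/0.0713 − 1.96) = 80.1%.

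**2. Chance imbalance and its effect.** The SD of the difference in shock prevalence between arms is sqrt(2q(1−q)/86). Multiplying by 1.96 gives the 95% limit of imbalance; multiplying that by d gives the shift in the unadjusted response difference.

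**3. Precision from adjustment on the risk-difference scale.** The variance within shock strata is 0.678 × 0.322 − q(1−q)d². The share of outcome variance explained is R² = q(1−q)d² / (0.678 × 0.322). Power is Φ(0.20 / sqrt(2 × within-variance / 86) − 1.96).

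| q | d | 95% imbalance (points) | 95% shift (points) | R² | Power, adjusted |
|---|---|---|---|---|---|
| 20% | 10 | 12.0 | 1.2 | 0.7% | 80.4% |
| 30% | 20 | 13.7 | 2.7 | 3.9% | 81.7% |
| 40% | 30 | 14.6 | 4.4 | 9.9% | 84.1% |

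Against 80.1% unadjusted, the gain is about 0.3 to 4 points of power.

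**4. Simulation check.** 200,000 trials per scenario, 86 per arm, simple randomisation (the minimisation was not mimicked), unadjusted test against a test stratified by shock.

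| q, d | Power, unadjusted | Power, stratified | Error at a true 20-point deficit, unadjusted | Same, stratified |
|---|---|---|---|---|
| 30%, 20 | 80.6% | 82.0% | 2.3% | 2.4% |
| 30%, 30 | 80.8% | 84.1% | 2.4% | 2.6% |
| 40%, 30 | 80.8% | 84.4% | 2.4% | 2.5% |

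Omitting shock therefore leaves the type I error of the unadjusted test at about its nominal 2.5%.

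**5. The gain does not carry over to the odds ratio.** Take q = 30%, d = 25 points, 90 per arm and no treatment effect. Response is 0.678 + 0.3 × 0.25 = 75.3% without shock and 50.3% with it, and the within-stratum variance is 0.2183 − 0.3 × 0.7 × 0.25² = 0.2052. The SE of the log odds ratio is sqrt(4 / (180 × 0.2183)) = 0.319 unadjusted and sqrt(4 / (180 × 0.2052)) = 0.329 adjusted. It rises. The precision gain belongs to a risk difference standardised from the model, not to the logistic coefficient.

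**The case against.** The case against has several parts.

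- **Chance imbalance is not a defect.** A reader might infer that an unequal share of shock patients would bias or invalidate the primary test. It would not. Chance imbalance is part of the sampling variation that the confidence interval and the type I error already allow for, and step 4 shows this. The objection stands. It strictly covers the randomised set, whereas the primary population is per-protocol. Exclusions related to severity that differ by arm could add imbalance that is not chance, but nothing in the document shows this will happen, and it is not counted here.
- **Shock is not ignored in every analysis.** A reader might infer that no planned analysis would reveal or remove a shock imbalance. The pre-defined shock subgroup compares the arms within shock strata, so those estimates are not distorted by it. This stands too. What that analysis does not give is one pooled adjusted estimate.
- **The covariate list may be open.** The word *including* sets a minimum, and a full list is commonly left to an analysis plan, which is not at hand. This is the strongest objection, and it keeps the point minor. The most that can be said is that the article names a covariate set without a severity measure.
- **SOFA may not be available at baseline.** Only the abbreviation is visible, so the argument rests on septic shock.
- **The benefit would not reach the primary test.** Correct: the fix touches secondary models only, and the primary power and interval stay as planned.

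**Conclusion.** The point holds in a limited form and is minor. The adjusted models as described contain no measure of acute severity, so no overall severity-adjusted estimate is pre-specified for clinical response or 28-day mortality, although septic shock has to be recorded for the subgroup analysis. The price is modest precision in a secondary estimate, and a severity-adjusted overall result that would have to be produced post hoc.

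The size rests wholly on the assumed 20-40% shock prevalence and 10-30 point response deficit: a shift of 1.2-4.4 points at the 95% limit of imbalance, well inside the 20-point margin, and 0.3-4 points of power for an adjusted risk difference. No figure is offered for mortality, because the document gives no mortality rate. The document does not support reading this as a fault in the primary analysis or as a need to change the minimisation.

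**What to change.** In the Statistical analysis section, or in the analysis plan if it fixes the covariates:

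1. Add septic shock status at randomisation to the covariates of the secondary adjusted models for clinical response and 28-day mortality. State the time point, since the article does not say when shock is classified for the subgroup and a covariate must be a baseline value.
2. Add baseline SOFA as well, if the schedule of assessments collects it at baseline.
3. Report a standardised (marginal) adjusted risk difference with its confidence interval beside the unadjusted primary difference. An adjusted odds ratio alone cannot be read against the 20-point margin and does not bring the precision gain.

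The cost is a few lines of text. Shock status is already needed for the subgroup analysis, the primary test and sample size are unchanged, and allocation is not touched. The wording should be settled before outcome data by arm are seen.
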